**LIST OF ABBREVIATIONS AND RELEVANT DEFINITIONS**

|                   |                                                                                                                                                                                                             |
|-------------------|-------------------------------------------------------------------------------------------------------------------------------------------------------------------------------------------------------------|
| ABR        | ABR form, General Assessment and Registration form, is the application form that is required for submission to the accredited Ethics Committee (In Dutch, ABR = Algemene Beoordeling en Registratie) |
| Anti-Xa    | Antifactor Xa                                                                                                                                                                                        |
| ATC-code   | Anatomical Therapeutic Chemical Classification System                                                                                                                                                |
| A-TEAM     | Antibiotic teams                                                                                                                                                                                     |
| AE         | Adverse Event                                                                                                                                                                                        |
| APTT       | Activated Partial Thromboplastin Time                                                                                                                                                                |
| AR         | Adverse Reaction                                                                                                                                                                                     |
| CA         | Competent Authority                                                                                                                                                                                  |
| CCMO       | Central Committee on Research Involving Human Subjects; in Dutch: Centrale Commissie Mensgebonden Onderzoek                                                                                          |
| CV         | Curriculum Vitae                                                                                                                                                                                     |
| DBC        | Diagnose Behandeling Combinatie                                                                                                                                                                      |
| DSMB       | Data Safety Monitoring Board                                                                                                                                                                         |
| DVT        | Deep vein thrombosis                                                                                                                                                                                 |
| dTT        | Diluted Thrombin Time                                                                                                                                                                                |
| eGFR       | Estimated Glomerular Filtration Rate                                                                                                                                                                 |
| EU         | European Union                                                                                                                                                                                       |
| EudraCT    | European drug regulatory affairs Clinical Trials                                                                                                                                                     |
| EQ5D score | EuroQol EQ5D score                                                                                                                                                                                   |
| GCP        | Good Clinical Practice                                                                                                                                                                               |
| HARM       | Hospital Admissions Related to Medication                                                                                                                                                            |
| Hb         | Hemoglobin                                                                                                                                                                                           |
| HT         | Hematocrit                                                                                                                                                                                           |
| IB         | Investigator's Brochure                                                                                                                                                                              |
| IC         | Informed Consent                                                                                                                                                                                     |
| IMP        | Investigational Medicinal Product                                                                                                                                                                    |
| IMPD       | Investigational Medicinal Product Dossier                                                                                                                                                            |
| INR        | International Normalized Ratio                                                                                                                                                                       |
| ISTH       | International Society on Thrombosis and Haemostasis                                                                                                                                                  |
| LOS        | Length of the hospital stay                                                                                                                                                                          |
| LSKA       | Landelijke Standaard Keten zorg Antistolling                                                                                                                                                         |
| MARS       | Medication Adherence Rating Scale                                                                                                                                                                    |
| METC       | Medical research ethics committee (MREC); in Dutch: Medisch Ethische Toetsing Commissie (METC)                                                                                                       |
| NOACs      | New oral anticoagulants                                                                                                                                                                              |
| PE         | Pulmonary embolism                                                                                                                                                                                   |
| PT         | Prothrombin time                                                                                                                                                                                     |
| (S)AE      | (Serious) Adverse Event                                                                                                                                                                              |
| SPC        | Summary of Product Characteristics (in Dutch: officiële productinformatie IB1-tekst)                                                                                                                 |

|                |                                                                                                                                                                                                                                                                                                                                           |
|----------------|-------------------------------------------------------------------------------------------------------------------------------------------------------------------------------------------------------------------------------------------------------------------------------------------------------------------------------------------|
| Sponsor | The sponsor is the party that commissions the organisation or performance of the research, for example a pharmaceutical company, academic hospital, scientific organisation or investigator. A party that provides funding for a study but does not commission it is not regarded as the sponsor, but referred to as a subsidising party. |
| S-TEAM  | Stollingsteam (antithrombotic team)                                                                                                                                                                                                                                                                                                       |
| SUSAR   | Suspected Unexpected Serious Adverse Reaction                                                                                                                                                                                                                                                                                             |
| TTR     | Time in therapeutic range                                                                                                                                                                                                                                                                                                                 |
| VKA     | Vitamin K antagonists                                                                                                                                                                                                                                                                                                                     |
| VTE     | Venous thromboembolism                                                                                                                                                                                                                                                                                                                    |
| Wbp     | Personal Data Protection Act (in Dutch: Wet Bescherming Persoonsgegevens)                                                                                                                                                                                                                                                                 |
| WMO     | Medical Research Involving Human Subjects Act (in Dutch: Wet Medisch-wetenschappelijk Onderzoek met Mensen)                                                                                                                                                                                                                               |

## SUMMARY

**Rationale:** Antithrombotic therapy carries high risks for patient safety. The Dutch HARM study showed that antithrombotics belong to the top 5 of medication involved in potentially preventable HARMs. Multidisciplinary teams have been proposed to improve the safety of antithrombotic therapy. However, most antithrombotic services are described mainly as pharmacist-led antithrombotic services in US hospitals that are predominantly aimed at warfarin dosing, which differs from the Dutch situation. At present the effect of a multidisciplinary antithrombotic team in the Dutch situation is unknown. The hypothesis is that the introduction of a multidisciplinary antithrombotic team (in Dutch 'Stollingsteam' or S-team) in hospital will improve the efficacy and safety of antithrombotic therapy.

**Objective:** The main objective of this study is to determine the effect of a multidisciplinary antithrombotic team ('S-team') on the frequency of a composite endpoint consisting of bleeding and thrombotic events. The secondary objectives are to study the effect of a S-team on the frequency of bleeding events, frequency of thrombotic events, severity of bleeding complications, length of hospital stay, readmissions, quality of life, adherence by the patient to the therapy, quality of care (patient satisfaction with antithrombotic therapy), adherence by the doctors to the hospital protocol, healthcare costs, all-cause mortality and percent time in therapeutic range of vitamin K antagonists.

**Study design:** An intervention study with a before- and after design.

**Study population:** Patients that are or will be treated with antithrombotics during admission to the university medical center Erasmus MC Rotterdam or general teaching hospital Reinier de Graaf Ziekenhuis Delft are included in the study. We aim to include 1834 patients, 917 patients in the pre-intervention phase and 917 patients in the post-intervention phase.

**Intervention:** The intervention consists of the implementation of the S-team.

**Main study parameters/endpoints:** Proportion of patients with a composite endpoint consisting of  $\geq 1$  bleeding (major bleeding and mild to moderate clinically relevant non-major bleeding) or  $\geq 1$  thrombotic event from time to start with antithrombotic medication (or hospitalization) until 3 months after hospitalization.

**Nature and extent of the burden and risks associated with participation, benefit and group relatedness:** At discharge the patient will be asked to fill out a consent form. By signing the consent form, the patient gives permission to retrieve patient data from the community pharmacist and the general practitioner. In addition, the patient receives four small questionnaires 3 months after hospitalization. It will take about 20 minutes to fill out the questionnaires.

## 1. INTRODUCTION AND RATIONALE

Antithrombotic therapy carries high risks for patient safety, as was clearly shown in the Dutch HARM - (Hospital Admissions Related to Medication) study and subsequent reports ('Monitor Zorggerelateerde Schade', from 2004, 2008 and 2012). The Dutch HARM study showed that antithrombotics belong to the top 5 of medication involved in potentially preventable HARMs.

In response to the HARM study, a multidisciplinary guideline was drafted to provide a standard for antithrombotic therapy and stress the importance of providing optimal care to patients on antithrombotic therapy: the 'Landelijke Standaard Ketenzorg Antistolling' (LSKA).

The mere publication of the LSKA does not guarantee its implementation. A parallel can be drawn with active policy on reduction of antibiotic resistance: all hospitals are involved in such policies, but still only recently the introduction of antibiotic stewardship was proposed in order to further enhance such policies. Multidisciplinary antibiotic teams (A-teams) are considered useful for optimization of therapy. Antithrombotics obviously carry more risk than antibiotics (bleeding and thrombotic complications), so it is logical to presume that multidisciplinary teams (in Dutch 'Stollingsteams' or S-teams) focusing on antithrombotics will be even more useful.

With non-vitamin K oral anticoagulants (NOACs) being marketed, it is unclear who will become responsible for optimization of their use. As vitamin K antagonists (VKAs) are the responsibility of Thrombosis Services, doctors are no longer used to monitor antithrombotic therapy, adherence and drug-drug interactions. Therefore, the supervision of therapy with NOACs may very well be insufficiently attended to. A solution would be to expand the work processes of the Thrombosis Services, but evidence on the effect of such expanded services is mostly lacking. Furthermore, with patients being hospitalized for increasingly shorter periods, optimization of transfer of anticoagulation therapy after discharge becomes of paramount importance.

Studies on the effect of a multidisciplinary antithrombotic team are scarce. Antithrombotic services are described mainly as pharmacist-led antithrombotic services in US hospitals that are predominantly aimed at warfarin dosing. This differs from the Dutch situation, where Thrombosis Services with a medical leader are responsible. In only 4 of 25 respondents of a survey such an antithrombotic service was multidisciplinary. One article describes an expanded antithrombotic stewardship, including both NOAC treatment and facilitating care after hospital discharge. It concerned a US one center pharmacist-led stewardship and the study included only a small retrospective control group of 12 patients. The majority of results were described for 409 patients monitored after implementation of the program. Also, the transition after discharge included only 34 patients, with 30 of them on warfarin therapy. Interventions consisted of changes to a more appropriate antithrombotic according to guidelines and dosing corrections. The length of hospital stay was reduced by 1.5 days and cost savings were \$270320 in 1.5 years. Discharge patient education and knowledge of patients is described in a few studies, but again mostly on warfarin. Given the known effect of patient education on adherence, patient education will be much more important for the NOAC therapy in which monitoring cannot be used to verify adherence.

The (lack of) implementation of the LSKA, and the shifting responsibilities regarding NOACs need solutions aiming at safe use of antithrombotics. The intervention in the present study consists of the implementation of an S-team. An S-team can be made responsible for LSKA implementation, can act as an expert team that can be consulted both from in- and outside the hospital, can take care of adequate handovers of patients discharged from hospital, and can improve patient education. A properly informed patient will more likely use antithrombotics safely and adherently, resulting in less complications.

At present the effectiveness of a multidisciplinary antithrombotic team is unknown. Therefore, the main objective of this study is to determine the effect of a multidisciplinary antithrombotic team ('S-team') on the frequency of bleeding and thrombotic events in two Dutch hospitals.

## 2. OBJECTIVES

### Primary Objective:

To determine the effect of a multidisciplinary antithrombotic team on the frequency of a composite endpoint consisting of bleeding and thrombotic events.

### Secondary Objective(s):

The following secondary objectives when a multidisciplinary antithrombotic team (S-team) is installed in the hospital are:

1. To determine the effect on frequency of bleeding events.
2. To determine the effect on frequency of thrombotic events.
3. To determine the effect on severity of bleeding complications.
4. To determine the effect on length of the hospital stay.
5. To determine the effect on percentage of (re)admissions caused by antithrombotic medication.
6. To determine the effect on quality of life, adherence by the patient to the therapy and quality of care (patient satisfaction with antithrombotic therapy).
7. To determine the effect on adherence to the hospital protocol.
8. To determine the effect on costs.
9. To determine the effect on all-cause mortality.
10. To determine the effect on percent time in therapeutic range of vitamin K antagonists.

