### 4.4 Sample size calculation

In studies major bleeding complications tend to occur in about 2-3% of all patients per year on antithrombotics, but in every day practice it seems this rate is at least 10%. Conservatively, we will presume a rate of 5%. Thrombotic events are estimated to occur in 3% of treated patients per year in studies. As trials form the ideal situation, we assume this is the rate we could achieve with the S-team and that the rate is 4% in the pre-intervention period. This results in a composite rate of 9% and we expect to decrease this to 2.5% bleeding events and 3% thrombotic events (composite 5.5%). With an alpha of 0.05 and power of 0.80 the required sample size will be 917 patients in the pre-intervention phase and 917 patients in the post-intervention phase. In order to account for drop-outs 1900 patients will be included.

In a (not yet published) study aiming at the development of a prediction rule for VKA-related International Normalized Ratio (INR) elevation from our Erasmus MC group 3800 patients using VKAs were included over 4 years. Thus within 9 months over 700 patients using VKAs will be admitted to the Erasmus MC alone. As we include another hospital and other antithrombotics as well, we expect that 9 months will be sufficient to recruit the required number of patients.

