#### 8.1.2 Secondary study parameters/endpoints

- Proportion of patients with  $\geq 1$  bleeding (major bleeding and mild to moderate clinically relevant non-major bleeding) event from time to start with antithrombotic medication (or hospitalization) until 3 months after hospitalization.
- Proportion of patients with  $\geq 1$  thrombotic event from time to start with antithrombotic medication (or hospitalization) until 3 months after hospitalization.
- Severity of bleeding complication
- Length of hospital stay (LOS)
- Percentage of readmissions within 3 months after discharge
- Patient related outcomes (quality of life, adherence of patient to therapy and patient satisfaction with the quality of care of the antithrombotic therapy)
- Adherence to the hospital protocol
- Healthcare costs (labor costs versus costs for bleeding/thrombotic events (including use of antidotes))
- All-cause mortality
- Percent time in therapeutic range of vitamin K antagonists during hospitalization and 3 months after discharge.

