### ***Severity of bleeding complication***

The ISTH/SSC proposed a bleeding assessment tool that facilitates the diagnosis of less symptomatic mild bleeding disorder and the grading of severity in patients with known inherited bleeding disorders. For each specific bleeding symptom, a score of 1 or more is classified as significant.

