### **10.2 Secondary study parameter(s)**

For the secondary outcomes linear or logistic regression analysis will be used, depending on the parameter.

To assess differences in patient characteristics for the two periods the appropriate test (t-test, Mann-Whitney U test or Pearson's chi-square test) will be used.

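### Severity of bleeding is worded as a property of a bleed, with no value for patients who do not bleed; a phase comparison among bleeders would condition on an outcome the S-team is meant to reduce, and can point the wrong way

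*Protocol*

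**What the plan says.** - Section 2, secondary objective 3: "To determine the effect on severity of bleeding complications". Secondary objective 1 is, separately, the effect on how often bleeding occurs.
- Section 8.1.2 lists the endpoint only as "Severity of bleeding complication". The bleeding and thrombosis endpoints above it in the same list are proportions of patients with at least one event, so their denominator is all patients. The severity endpoint has no denominator.
- The severity paragraph in section 8.3.1 refers to the ISTH/SSC bleeding assessment tool: "For each specific bleeding symptom, a score of 1 or more is classified as significant". It assigns no value to a patient without a bleed. The case report form (Table 3) has one item for severity, taken from the medical record.
- Section 10.2: "For the secondary outcomes linear or logistic regression analysis will be used, depending on the parameter". It names no analysis set for severity.
- Section 4.4 assumes that bleeding falls from 5% before to 2.5% after the intervention. The 5% follows a sentence on major bleeding per year: "In studies major bleeding complications tend to occur in about 2-3% of all patients per year on antithrombotics".

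**The concern.** A severity score attached to a bleed exists only where there was a bleed. If the regression is run on those patients, the two groups compared are the patients who bled under usual care and the patients who still bled with the S-team active. The second group has been selected by the intervention's own effect. The phase difference then mixes any change in how severe bleeds are with a change in which bleeds occur. Adjustment for baseline covariates does not in general remove this.

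A programme that mainly prevents milder bleeds would leave a more severe remainder. The analysis could then report worse severity although bleeding had become rarer in every grade, and the stated objective would not be answered. The problem does not depend on the grading tool, since any tool applied to bleeders only behaves in the same way.

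**Working it through.** **The plan's own figure.** Composite 9% versus 5.5%, alpha 0.05 two-sided, power 0.80. The pooled-variance formula gives n = 861 per phase. The continuity correction, n/4 × [1 + √(1 + 4/(n × 0.035))]², gives 917, which matches section 4.4. The rates below therefore belong to the calculation that produced 917.

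**Bleeders on those rates.** 917 × 0.05 = 45.9, about 46 before. 917 × 0.025 = 22.9, about 23 after. Some 23 bleeds are prevented.

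**When the direction reverses.** Let f be the major share among the 46 bleeders before and g the major share among the 23 prevented bleeds. The major share among the remaining bleeders is (46f − 23g)/23 = 2f − g. This exceeds f whenever g < f, that is, whenever prevented bleeds are milder than average. Major bleeds over all patients still fall whenever g > 0. The protocol gives neither f nor g, so both are assumptions here.

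**Illustration with f = 50%** (23 major and 23 non-major before). Among bleeders the odds ratio is (major/non-major after)/(23/23), with p from Fisher's exact test. Over all patients it is [major after/(917 − major after)]/(23/894), with a Woolf 95% interval, exp(ln OR ± 1.96 × √(sum of the four reciprocal cell counts)).

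| Prevention | Major / non-major after | Major share among bleeders | OR among bleeders (p) | Major, all patients | OR for major, all patients (95% CI) |
|---|---|---|---|---|---|
| Near proportional | 12 / 11 | 52% | 1.09 (1.0) | 2.5% to 1.3% | 0.52 (0.25 to 1.04) |
| Moderately selective | 15 / 8 | 65% | 1.88 (0.31) | 2.5% to 1.6% | 0.65 (0.34 to 1.25) |
| Highly selective | 20 / 3 | 87% | 6.67 (0.0035) | 2.5% to 2.2% | 0.87 (0.47 to 1.59) |

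In the last row non-major bleeds also fall, from 23/917 = 2.5% to 3/917 = 0.3%. Both grades become rarer while the comparison among bleeders reads as harm.

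**A second starting share.** With f = 40% and g = 20%, major bleeds go from 18.4 to 13.8 (2.0% to 1.5% of all patients), while the major share among bleeders rises from 40% to 60%. With f = 40% and g from 10% to 50%, the share afterwards runs from 70% to 30%.

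**Precision among bleeders.** With 46 and 23 patients, 80% power needs a difference of (1.96 + 0.84) × √(1/46 + 1/23) = 0.72 SD.

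**Range for the number of bleeders.** If 5% and 2.5% are annual rates and only three months count, there are 917 × 0.05/4 = 11 and 917 × 0.025/4 = 6 bleeders. If non-major bleeds come on top of the 5%, there are more. With twice as many (46/46 before, 34/12 after), the odds ratio among bleeders is 34/12 = 2.83 (p=0.010).

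**Would a proportional-odds model over all patients help?** On none/non-major/major it gives common odds ratios of 0.488, 0.490 and 0.494 for the three rows of the table. The plain odds ratio for any bleed is (23/894)/(46/871) = 0.487 each time, so the model nearly repeats bleeding frequency. If major bleeds rose from 23 to 28 and non-major bleeds fell from 23 to 0, it would give 0.61 (0.38 to 0.98), although the odds ratio for major bleeding is (28/889)/(23/894) = 1.22.

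**The case against.** The strongest reply is that the protocol never restricts the severity analysis to bleeders. Section 10.2 names no analysis set, a significance threshold of 1 leaves room for a score of zero, and a logistic regression of major bleeding over all patients would satisfy section 10.2 as it stands. The statistical analysis plan, which is not at hand, may settle this. That stands against any claim that the protocol prescribes a bleeders-only regression. It does not remove the point, because whose severity is compared is part of the endpoint's definition. The protocol words it as an attribute of a complication, in contrast to the patient proportions listed beside it. The zero is only an inference from the threshold.

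Three further objections also hold in part.

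- A reader might infer that a misleading significant result is likely. The documents do not support that. The split by grade is assumed, and only the highly selective scenario is significant. In that scenario the fall in major bleeds, 23 to 20, is itself no demonstrable change (p=0.76).
- A reader might take 46 and 23 as the plan's forecast for this endpoint. The 5% comes from annual major-bleeding rates, whereas the endpoint adds clinically relevant non-major bleeding and ends three months after hospitalization. The selection mechanism does not depend on these counts, but the size of the illustration does.
- Bleeding frequency is reported separately, so a reader would see that bleeding fell. This limits the damage but does not make the severity comparison interpretable.

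**Conclusion.** The point holds in a conditional form. As worded, severity is defined only for patients who bleed. If phases are compared among them, the contrast conditions on an outcome that the S-team is expected to halve. It moves towards worse severity whenever prevented bleeds are milder than average, even with every grade rarer.

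On the sample-size rates and an assumed 50% major share before, the odds ratio among bleeders runs from 1.09 to 6.67, against 0.52 to 0.87 for major bleeding over all patients. These figures illustrate the mechanism and do not forecast the result. They rest on 46 and 23 bleeders, the assumed split, and the assumed selectivity of prevention. If prevented bleeds are of average severity, the distortion is close to nil.

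This is one of ten secondary objectives and leaves the primary analysis untouched. It should be corrected because the correction is cheap and the alternative is a result that could suggest harm from a beneficial programme.

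**What to change.** In section 8.1.2, define severity for every included patient as the worst bleeding grade during follow-up: none, non-major, or major including fatal. Section 8.3.1 already defines these grades.

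In section 10.2, state that the proportion of all included patients with major bleeding is compared between phases by the logistic regression already planned, and that counts and proportions per grade are reported for each phase. Present the distribution of grades, or the tool score, among bleeders as description only, without a between-phase test.

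Do not make a proportional-odds model the main analysis, since it would be driven almost wholly by bleeding frequency and could hide a rise in major bleeds.

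The cost is about one sentence in each section and no extra data. The result is no longer the average severity per bleed, and major-bleed counts will be small, so the estimate will be imprecise, as the intervals in the table show.
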